### Recruitment

The study will be disseminated through the existing communication channels of the participating TU (mailing to the email addresses of the existing lists, blog/web, EIR websites, teaching sessions, or face-to-face meetings). After the aim of the study is explained, the professionals will be invited to take part in the study and must fill out both the commitment and informed consent forms.

### Assignment of interventions and randomisation

Cluster randomisation will be used, and each TU will be a cluster. Subject selection will be performed in each cluster and stratified by type of professional (66 tutors vs. 66 residents) between the CG (2 TU) and the two intervention groups (4 TU).

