## Methods/design

### Study design (Fig. 1)

The MINDUUDD study comprises an open-label, pragmatic, non-inferiority, multicentre, cluster randomised controlled trial with three parallel arms. The participating UUDDs will be randomised to one of the three study groups. Interventions will last for 8 weeks for one group (EG8) and 4 weeks (EG4) for the other. In both groups, there will be a follow-up at three months to check the maintenance of the programs’ effect. The control group (CG) will be reassessed 8 weeks after the start of the fieldwork.

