### Intervention scheme

The interventions will be based on the MBSR programme [8–10] designed by Jon Kabat-Zinn and used at the Medical Center of the University of Massachusetts. Certain self-compassion practices of the Mindful Self-Compassion (MSC) programme [17–19] (Table 1) will be incorporated. The programmes to be tested will be adapted to the participating health care group and will differ by their duration and time dedicated to the tasks [30]:Standard program: The format will be 8 weekly sessions of 2.5 h each. Participants must practice at home for 30 min a day.Abbreviated program: The format will be 4 weekly sessions of 2.5 h each. Participants must practice at home for 15 min a day.

**Table 1 Tab1:** Mindfulness and self-compassion training programs

	8-WEEK PROGRAM	4-WEEK PROGRAM
PRESENTATION BASELINE MEASUREMENT	General explanation, objectives, schedule. Pre-intervention measurements: general data, FFMQ, SCS, PSQ, MBI-GS, JSPE, GADS, AES questionnaires.	
1st SESSION	Raisin exercise. What is mindfulness? Practice: body scan. Informal practice: brushing.teeth Task: 30′ body scan.	Raisin exercise. What is mindfulness? Managing thoughts and emotions during practice. Practice: body scan. Informal practice: brushing.teeth Task: 30′ body scan.
2nd SESSION	Concepts: stress and burnout Practice: mindful breathing (sitting). 3-min mindfulness practice. Informal practice: mindful shower, 3′. Task: 30′ body scan + 10′ sitting.	Concepts: stress and burnout. Primary and secondary suffering. Practice: mindful breathing (sitting). 3-min mindfulness practice. Informal practice: mindful shower, 3′. Task: 30′ body scan + 10′ sitting.
3rd SESSION	Posture. Being versus doing. Managing thoughts and emotions during practice. Practice: yoga (standing meditation). Informal practice: washing the dishes, 3′. Task: alternating body scan or yoga + 15′ sitting.	Unconditional love (metta). Compassion. Practice: conscious movements. Metta for oneself and for others. Informal practice: washing the dishes, 3′, thank you letter. Task: alternating body scan or yoga + 15′ sitting.

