3) CG: without intervention. Participants will only receive a 1-h information session explaining the study design and their role in the study and inviting them to complete the expected data at two time points (coinciding with the interventions in the EG8). They will pledge not to receive any intervention and will be asked not to participate in the practice of any session of full attention or meditation techniques during the study period. After the fieldwork, they will be offered the opportunity to participate in the abbreviated training programme.

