### Data collection and data management

The measurements will be taken at three time points: 1) Pre-intervention (initial or baseline; one week before the interventions begin, participants from all groups will be invited to a face-to-face meeting); 2) Post-intervention (final, one month for EG4 and two months for EG8, and simultaneously with the latter for CG participants); and 3) Three months after the interventions, at which time participants of EG4 and EG8 will be reconvened for a face-to-face session.

To measure adherence to the training programs, the sessions attended by the participants will be continuously monitored and followed up, and students must write in a personal notebook or journal whether they did the exercises at home and show it to the instructor in each session for supervision.

The data obtained (data collection notebook and questionnaires) will be collected and sent to the coordinating headquarters for further processing, debugging, and statistical analysis. Double data entry will be used for all questionnaires to keep the rate of data errors very low.

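### Baseline self-report is likely taken with the arm known, and nothing states that consent and selection within a Teaching Unit come before its allocation is disclosed

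*Protocol article*

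**What the plan says.** Study design describes an "open-label, pragmatic, non-inferiority, multicentre, cluster randomised controlled trial with three parallel arms". Under Assignment of interventions and randomisation, "Cluster randomisation will be used, and each TU will be a cluster", followed by "Subject selection will be performed in each cluster and stratified by type of professional", with 66 tutors and 66 residents divided between two control TUs and the four TUs of the two intervention groups. Recruitment says that, once the study's aim has been explained, "the professionals will be invited to take part in the study and must fill out both the commitment and informed consent forms".

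The baseline is described in four places:

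- **Outcomes and measures** has the pre-intervention questionnaire completed at recruitment.
- **Data collection and data management** places it later: "one week before the interventions begin, participants from all groups will be invited to a face-to-face meeting".
- **Table 1**, presentation and baseline row: "General explanation, objectives, schedule. Pre-intervention measurements: general data", followed by the questionnaires.
- **Intervention scheme**, control group: participants get a one-hour session that covers the design and their own role and asks them for data at two time points. The next sentence adds: "They will pledge not to receive any intervention and will be asked not to participate in the practice" of meditation techniques during the study.

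Statistical methods compares pre-post differences between groups and then fits an adjusted multilevel regression.

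**The concern.** In an open-label cluster trial everyone in a TU shares one arm, so once the allocation is known locally it can be known to every invitee. Two things then depend on the order of events.

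**Baseline.** All the primary outcomes are self-reported questionnaires. A person who knows that a course is about to start, or who has just promised to do without one, may answer differently from someone who does not know. The group comparison uses pre-post differences, so a baseline that has itself been moved by knowledge of the arm goes straight into the effect estimate.

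**Selection.** The arms ask very different things of participants: eight sessions with 30 minutes of daily practice, four sessions with 15 minutes, or no programme until after the fieldwork. If people volunteer knowing which applies, the arms may differ in motivation or stress. With two TUs per arm, randomisation cannot be relied on to even this out. The listed covariates contain no motivation measure, and Strengths and limitations discusses selection through dropout but not through recruitment.

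**Working it through.** **Step 1: when baseline is taken.** Controls are measured only twice, before the programmes and when EG8 finishes (Study design; Data collection). The two time points named in the control session therefore include baseline. The session that asks for baseline data is thus the one that explains the participant's role as a control. The pledge to receive no intervention makes sense only for someone who knows the arm.

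For the intervention arms the evidence is weaker. Baseline comes a week before the start, from participants described by group, and the Table 1 row lists the schedule ahead of the questionnaires.

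The recruitment-time and week-before statements agree only if recruitment itself takes place at that meeting, when groups are already spoken of. If recruitment is earlier, one of the two is wrong. Neither version says that the arm is withheld.

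**Step 2: when selection is made.** The assignment section gives structure (clusters, strata, TUs per side) and no sequence. Recruitment mentions explaining the aim and does not mention the arm. No section says that the TU's arm is concealed until consent and selection are complete.

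**Step 3: the plan's own inputs.** The point rests on no stated figure, but the inputs used below reproduce. For 15 points, SD 20, two-sided 5% and 80% power, n = 2 × (1.96 + 0.842)² × 20² / 15² = 27.9, so 28. Allowing for 25% loss, 28 / 0.75 = 37.3, so 38, as stated. The design effect at cluster size 15 is 1 + 14 × 0.05 = 1.70, as stated. At the planned 22 per TU it is 1 + 21 × 0.05 = 2.05.

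**Step 4: what a shift would do (illustration).** The article gives no size for an arm-related shift. Assume a spurious between-arm difference b in FFMQ change, and an SD of 20 for the analysed quantity. The plan's SD of 20 is for the score; a change score has the same SD if the pre-post correlation is 0.5. With 44 per arm:

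- SE without clustering = 20 × √(2/44) = 4.26
- SE with design effect 2.05 = 20 × √(2 × 2.05/44) = 6.11
- Actual error = Φ(b/SE − 1.96) + Φ(−b/SE − 1.96)

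| Assumed b (points) | Share of the 15-point target | Error, no clustering | Error, ICC 0.05 |
|---|---|---|---|
| 2 (0.1 SD) | 13% | 7.6% | 6.2% |
| 5 (0.25 SD) | 33% | 21.6% | 13.0% |
| 7.5 (0.375 SD) | 50% | 42.0% | 23.3% |
| 10 (0.5 SD) | 67% | 65.0% | 37.4% |

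A larger sample does not shrink b; it reduces the SE and makes a false finding more likely.

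**The case against.** The strongest reply is that the article never gives the order of events, and that a condensed article may leave it to the full protocol. The assignment section contains no word placing selection after randomisation. Recruitment through general TU channels, with only the aim explained, followed by consent and a questionnaire at recruitment, is close to the sequence one would want. Reference to participants from all groups may be no more than the authors' way of saying everyone. In Table 1 as extracted, the baseline entry fills one cell and leaves the 4-week cell blank, which fits a merged cell for a common presentation. Word order in a cell does not prove that the explanation came first. Controls are also offered the abbreviated programme afterwards, which narrows the difference in appeal between arms.

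Much of this stands against the selection half. A reader might infer that people volunteer knowing their arm; the documents do not show it. A reader might also take 132/802 = 16.5% as a volunteer rate. It is not: 132 is the planned sample and 802 the stated population before exclusions. Further, a stable difference in FFMQ level produced by selection would largely cancel in a change score. Only the part linked to how people respond or adhere would remain.

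The reply does not dispose of the baseline half. The control session is described positively, not left unsaid, and the conflict over when baseline is taken lies within the article. Nor would adjustment for baseline repair a baseline already moved by knowledge of the arm.

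**Conclusion.** The concern holds for the baseline and remains open for selection. As written, controls are likely to give baseline self-reports with their arm known or being disclosed, and intervention participants may well do so too. The order of pledge and questionnaire is not stated, so this is likely rather than certain. Differential volunteering by arm is possible because no section rules it out, but it is not shown, and the documents supply nothing from which to size it.

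The error rates above rest on an assumed shift and on an SD of 20 for change. They show only that a shift well below the 15-point target would matter. A shift that persisted unchanged to the later measurement would cancel; the harm comes from the part peculiar to baseline. This is worth settling before enrolment, because no later analysis can recover an uncontaminated baseline.

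**What to change.** Reconcile the control-group paragraph, Outcomes and measures, Assignment of interventions and randomisation, and Data collection so that they give one sequence:

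1. Invite professionals in all six TUs with one common text that describes all three possible arms.
2. Obtain the consent and commitment forms and the baseline questionnaires.
3. Close the list of 22 participants in each TU.
4. Only then randomise the TUs, or reveal an allocation held elsewhere.
5. Hold the arm-specific session and take the control pledge after that.
6. Analyse everyone on the closed lists by intention to treat.

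If the full protocol already works this way, a sentence saying so and aligned wording in the four sections is enough.

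The steps are already planned, so the cost is mainly reordering, and the sample size is unchanged. Sessions can be scheduled only once baseline has closed. Some participants may withdraw on learning their arm; they stay in the intention-to-treat set and draw on the 25% loss allowance. The change does not remove the influence of open-label knowledge on the later questionnaires.

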### Data collection and data management

The measurements will be taken at three time points: 1) Pre-intervention (initial or baseline; one week before the interventions begin, participants from all groups will be invited to a face-to-face meeting); 2) Post-intervention (final, one month for EG4 and two months for EG8, and simultaneously with the latter for CG participants); and 3) Three months after the interventions, at which time participants of EG4 and EG8 will be reconvened for a face-to-face session.

To measure adherence to the training programs, the sessions attended by the participants will be continuously monitored and followed up, and students must write in a personal notebook or journal whether they did the exercises at home and show it to the instructor in each session for supervision.

The data obtained (data collection notebook and questionnaires) will be collected and sent to the coordinating headquarters for further processing, debugging, and statistical analysis. Double data entry will be used for all questionnaires to keep the rate of data errors very low.

### Statistical methods

The descriptive statistics of baseline characteristics of study participants and of questionnaire results—both before and after the intervention—will include means, standard deviations and ranges, medians and interquartile ranges, or frequencies and percentages, according to the variables. The fit of quantitative variables to the normal distribution will be checked by the Kolmogorov-Smirnov test. Prior to testing the effectiveness of the intervention, appropriate statistical tests will be used to examine possible baseline differences between groups (age, sex, time worked, profession, year of residency, previous mindfulness training). A per-protocol analysis will be performed in which all subjects who have completed at least 6 of the 8 sessions in EG8, or 3 of the 4 sessions in EG4, will be considered. All signalment analyses will be intention-to-treat in order to control for non-random dropout effects. Patterns of missing values ​​will be inspected and, if applicable, replaced using appropriate statistical methods.

To compare pre- and post-intervention results, a bivariate analysis will be performed, using Student’s t-test or the Wilcoxon test to compare related samples. Pre-post differences in the results of the questionnaires between the groups will be compared using ANOVA for repeated measures. Finally, a multivariate analysis will verify the effect of the interventions, adjusting for presumably predictive and/or confounding variables. To accomplish this, a multilevel linear regression will be used. The level of statistical significance will be set at *p* < 0.05 for all statistics. The analyses will be performed with SPSS version 17.0 and MLwiN version 3.00 software.

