## Objective

The objective of the MINDUUDD study is to evaluate the effect of a mindfulness and self-compassion training programme on the levels of work stress and burnout in residents and tutors of Family and Community Medicine and Nursing. This study is based on the hypothesis that an abbreviated 4-session programme of mindfulness and self-compassion is at least as effective as the standard 8-session programme to increase mindfulness and reduce the levels of work stress and burnout of AP residents and tutors.

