### Sample size

To calculate the sample size, we have drawn on a previous study [25], using as an outcome variable the mean FFMQ score [31]; accepting an alpha risk of 0.05 and a beta risk of 0.2, in a bilateral contrast, 38 subjects are required in each group to detect a difference ≥ 15 points in the FFMQ scale between both experimental groups (EG4 and EG8) and the CG. It is assumed that the common standard deviation is 20. A loss or withdrawal rate of 25% has been estimated [43]. Because this is a cluster randomisation study, we have considered the design effect. The design effect multiplies the sample size by a factor ranging from 1.5 to 3 to achieve the same power, depending on the relationship between intra- and intergroup variance [44]. Estimates of the intra-cluster correlation coefficient (ICC) in randomised clinical trials in AP are generally < 0.05 [45]. This ICC, for a cluster size of 15, results in a design effect corresponding to a factor of 1.7. Assuming this value, the final study sample size would be at least 130 subjects. One hundred and thirty-two (132) professionals will be included, 44 in each comparison group, 22 for each teaching unit.

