### Strengths and limitations

With the cluster randomisation method, we expect to minimise the Hawthorne effect (contamination bias) in the intervention study. Withdrawals or losses may occur, which would cause a selection bias because the characteristics of the non-responders may differ from those of the responders. Due to the experience of the instructors in charge, adherence is likely to be very high at the beginning of the training program, but the loss rate thereafter could reach 20%. To lessen this problem, the sample size was increased by 25% [44]. In addition, to minimise and control this effect, from the statistical point of view, an intention-to-treat analysis will be performed in addition to the per-protocol analysis.

The questionnaires to be used are validated for the Spanish population and will be filled out anonymously (an identification code will be assigned to match those completed before and after the intervention), so we expect no problems of validity and reliability leading to important information biases.

Although the CG does not perform any type of intervention, this study does not ensure that it will remain inactive throughout the fieldwork period, which may minimise the differences in the expected results when comparing this group with the intervention groups.

To verify that the effect of the intervention programmes lasts over time, a measurement will be taken three months after their application. Although the ideal would be farther in the future, this distance is not feasible given that some participants will conclude their training period soon after completing the study, making it difficult to recruit them afterwards.

Our aim is to incorporate and extend the practice of mindfulness to the work, teaching, and care activities of health professionals—counting on the evidence to be found in this trial and contribute to increasing and complementing the countless existing tests that have been applied in other work sectors, both public and private.

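### Intention-to-treat is set for all comparisons on dropout grounds, and the planned per-protocol analysis has no role in the EG4 versus EG8 non-inferiority conclusion

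*Protocol article*

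**What the plan says.** The Study design section describes an "open-label, pragmatic, non-inferiority, multicentre, cluster randomised controlled trial with three parallel arms". The Objective section gives the hypothesis that "an abbreviated 4-session programme of mindfulness and self-compassion is at least as effective as the standard 8-session programme".

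Statistical methods plans both analysis sets. First comes per-protocol: "A per-protocol analysis will be performed in which all subjects who have completed at least 6 of the 8 sessions in EG8", or 3 of 4 in EG4. The next sentence reads "All signalment analyses will be intention-to-treat in order to control for non-random dropout effects". The word *signalment* is unclear; from context it appears to mean significance. Strengths and limitations, after discussing withdrawals and losses, adds that "an intention-to-treat analysis will be performed in addition to the per-protocol analysis".

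No sentence says which set decides EG4 versus EG8, or what follows if the two disagree. The planned tests are difference tests at p < 0.05. The sample size is set "to detect a difference ≥ 15 points in the FFMQ scale between both experimental groups (EG4 and EG8) and the CG", that is, for superiority over control.

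**The concern.** For EG4 or EG8 against control, intention-to-treat is the cautious choice: people who miss sessions pull the active arm towards control and make a benefit harder to show. For EG4 against EG8 the same feature can work the other way. If non-attendance makes the two arms more alike, the observed difference shrinks, and a shrunken difference is what a non-inferiority claim needs.

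The reason given for intention-to-treat is non-random dropout. That concerns missing people, not missed sessions, so dilution by non-attendance does not appear to have been considered when the rule was written. The article says that adoption of the short course into curricula and training plans would follow if it proves at least as effective. That conclusion could rest partly on non-attendance, while the one analysis able to show this has no say in it.

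**Working it through.** **The plan's own figure.** Inputs from Sample size: "accepting an alpha risk of 0.05 and a beta risk of 0.2, in a bilateral contrast", a difference of 15 FFMQ points, SD 20, 25% loss. n = 2 × (1.96 + 0.842)² × (20/15)² = 27.9, so 28 per group; 28/0.75 = 37.3, so 38. The stated 38 reproduces. It concerns each experimental arm against control and sets no margin for EG4 versus EG8.

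**Dilution of the EG8-EG4 difference.** Inputs from the article: the per-protocol thresholds (6 of 8, 3 of 4). Assumptions of mine: sessions are attended independently with the same probability p in both arms; D8 and D4 are the full-programme gains, with D8 − D4 = 10.

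Completer shares are c8 = P(at least 6 of 8) and c4 = P(at least 3 of 4), both binomial. Three assumptions about non-completers:

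- A: they gain nothing in either arm, with D8 = 15 and D4 = 5. Observed difference = 15·c8 − 5·c4.
- B: EG8 non-completers get the EG4 gain, and missed EG4 sessions cost nothing. Observed difference = 10·c8.
- C: EG8 non-completers get the EG4 gain, and EG4 non-completers gain nothing. Observed difference = 10·c8 + (1 − c4)·D4, for D4 = 5, 10 or 15.

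| p | c8 | c4 | A | B | C, D4 = 5 | C, D4 = 10 | C, D4 = 15 |
|---|---|---|---|---|---|---|---|
| 0.70 | 0.5518 | 0.6517 | 5.0 | 5.5 | 7.3 | 9.0 | 10.7 |
| 0.75 | 0.6785 | 0.7383 | 6.5 | 6.8 | 8.1 | 9.4 | 10.7 |
| 0.80 | 0.7969 | 0.8192 | 7.9 | 8.0 | 8.9 | 9.8 | 10.7 |
| 0.85 | 0.8948 | 0.8905 | 9.0 | 8.9 | 9.5 | 10.0 | 10.6 |

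At p = 0.70, for example: A = 15 × 0.5518 − 5 × 0.6517 = 5.0; C with D4 = 15 is 5.518 + 0.3483 × 15 = 10.7.

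**Effect on a false non-inferiority claim.** Further assumptions: 44 per arm, SD 20, the article's design effect of 1.7, a one-sided 0.025 bound, a normal approximation, D8 = 15, no gain in non-adherent people, and a true full-adherence difference exactly equal to the margin M. SE = 20 × √(2 × 1.7/44) = 5.56. The probability of the claim is Φ((M − d)/SE − 1.96), where d is the intention-to-treat difference.

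| Non-adherence | M = 5 | M = 7.5 | M = 10 |
|---|---|---|---|
| none | 0.025 | 0.025 | 0.025 |
| 25% in both arms | 0.0414 | 0.0523 | 0.0655 |
| 25% in EG8 only | 0.0993 | 0.0993 | 0.0993 |
| 25% in EG4 only | 0.0080 | 0.0108 | 0.0145 |

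For M = 10 with 25% in both arms, d = 0.75 × 10 = 7.5 and Φ(2.5/5.56 − 1.96) = 0.0655. If the programmes are truly equal and adherence is equal, the difference stays at zero and no bias arises.

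**The case against.** **The direction is not fixed.** A reader might infer that intention-to-treat necessarily favours the hypothesis. The documents do not support that. Missed EG4 sessions act the other way, as scenario C and the last row of the second table show, and the article gives no attendance by arm. Nor does Table 1 support treating someone who leaves EG8 halfway as having had the EG4 course: EG4 reaches compassion and values in sessions 3 and 4, EG8 only in sessions 6 and 7. This objection stands in full, so the point is that the bias can occur, not that it will.

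**Intention-to-treat is legitimate here.** The trial is pragmatic, and the Discussion argues that shorter courses improve adherence, so lower attendance at the longer course may be part of the effect of interest. Per-protocol alone would be open to selection. This also stands. It argues for keeping intention-to-treat, but not for letting it decide alone.

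**Two stronger readings fail.** One might see a contradiction between Statistical methods and Strengths and limitations, but both plan both analyses and neither ranks them. One might call the attendance thresholds unequal, but both are 75%, and the completer shares differ little at 80% attendance or above. It would also be too strong to say the article explicitly makes intention-to-treat the deciding analysis, because that rests on an unclear word.

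**An article may leave the ranking of analysis sets to the full protocol or SAP.** True of silence. Here the article states a rule for all comparisons and gives a reason that does not fit the non-inferiority design it declares.

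**Conclusion.** The point holds in a limited form. The stated rule and its reason fit superiority over control, and the planned per-protocol set has no role in the EG4 versus EG8 conclusion. At an assumed 70% attendance per session, a true 10-point deficit would appear as anything from about 5 to 10.7 points; at 85%, about 9 to 10.6. In the second illustration, the chance of a false non-inferiority claim moves from 0.025 to between 0.008 and about 0.10, depending on which arm is poorly attended.

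These figures rest on assumed attendance, gains and margins that are not in the article, so they show sensitivity and do not forecast a bias. A rule requiring agreement can be applied only once a margin and a confidence-bound criterion exist. Their absence is the more basic gap, and adding a margin alone would not settle which analysis set decides.

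**What to change.** In Statistical methods, state the rule separately for each question:

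- EG4 versus EG8: non-inferiority is declared only if the confidence intervals for the difference in both the intention-to-treat and the per-protocol analysis exclude a pre-stated, justified margin. If the two disagree, it is not declared.
- EG4 and EG8 versus control: intention-to-treat alone decides.

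Add the margin and the confidence level, and replace the unclear word *signalment*.

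The cost is small. Both analyses are already planned, and Data collection and data management already provides for monitoring attendance. The downside is that the claim becomes somewhat harder to make. Before any loss to follow-up, 70% attendance would leave about 44 × 0.552 = 24 people in EG8 and 44 × 0.652 = 29 in EG4 for the per-protocol analysis; 85% attendance would leave about 39 in each.

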**Methods:**

The MINDUDD study is a multicentre cluster randomised controlled trial with three parallel arms. Six Teaching Units will be randomised to one of the three study groups: 1) Experimental Group-8 (EG8); 2) Experimental Group-4 (EG4) Control group (CG). At least 132 subjects will participate (66 tutors/66 residents), 44 in the EG8, 44 in the EG4, and 44 in the CG. Interventions will be based on the Mindfulness-Based Stress Reduction (MBSR) program, including some self-compassion practices of the Mindful Self-Compassion (MSC) programme. The EG8 intervention will be implemented during 8 weekly face-to-face sessions of 2.5 h each, while the EG4 intervention will consist of 4 sessions of 2.5 h each. The participants will have to practice at home for 30 min/day in the EG8 and 15 min/day in the EG4. The Five Facet Mindfulness Questionnaire (FFMQ), Self-Compassion Scale (SCS), Perceived Stress Questionnaire (PSQ), Maslach Burnout Inventory (MBI), Jefferson Scale of Physician Empathy (JSPE), and Goldberg Anxiety-Depression Scale (GADS) will be administered. Measurements will be taken at baseline, at the end of the programs, and at three months after completion. The effect of the interventions will be evaluated by bivariate and multivariate analyses (Multiple Linear Regression).

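### The repeated-measures ANOVA between arms has no Teaching Unit term although Teaching Units are randomised, and the abstract and Methods name different final models

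*Protocol article*

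**What the plan says.** The unit of randomisation is clear. Under Assignment of interventions and randomisation: "Cluster randomisation will be used, and each TU will be a cluster". There are six TUs. Two go to control and four to the two intervention arms, with 44 people per arm and 22 per TU, so there are two TUs per arm.

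The Sample size section acknowledges clustering. It says ICCs in primary care trials usually lie below 0.05 and takes a design effect of 1.7 for clusters of 15.

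The Statistical methods section starts with paired tests of change over time. It then states: "Pre-post differences in the results of the questionnaires between the groups will be compared using ANOVA for repeated measures". An adjusted analysis comes last: "To accomplish this, a multilevel linear regression will be used", with MLwiN named beside SPSS. The 0.05 significance level applies to every test. The abstract describes the analysis differently: effects will be "evaluated by bivariate and multivariate analyses (Multiple Linear Regression").

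**The concern.** With two time points, the group-by-time test in a repeated-measures ANOVA is the same as a one-way ANOVA on individual change scores. Without a TU term, its error variance leaves out the variation between TUs, which is the variation that randomising TUs exposes the comparison to. The test therefore contradicts the premise on which the sample was sized.

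Two things are at stake. Comparisons with control would be declared significant too often. The EG4-EG8 interval would also be too narrow, which matters because the Study design section calls the trial non-inferiority, and a falsely narrow interval can falsely support that claim.

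The abstract adds to the problem. Multiple linear regression, as ordinarily understood, has no cluster level, whereas the model in the Methods does.

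**Working it through.** **Inputs from the Sample size section.** Two-sided alpha 0.05, power 0.80, a 15-point FFMQ difference, SD 20, 25% loss, and a stated 38 per group. Also ICC 0.05 as an upper value, cluster size 15 for planning and 22 per TU enrolled.

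**The plan's own figures.**
- n per group = 2 × (1.96 + 0.84)² × 20² / 15² = 27.9, i.e. 28. With 25% loss, 28 / 0.75 = 37.3, i.e. 38. This reproduces.
- Design effect DE = 1 + (15 − 1) × 0.05 = 1.70. This reproduces.
- At the 22 per TU actually planned, DE = 1 + 21 × 0.05 = 2.05. After 25% loss (16.5 per TU), DE = 1 + 15.5 × 0.05 = 1.775.

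**Type I error of a test that ignores TU.** The true variance of an arm contrast is DE times the variance the test uses. So:
- pairwise contrast: 2 × [1 − Φ(1.96 / √DE)]
- three-arm test (2 df): P(χ²₂ > 5.99 / DE) = exp(−5.99 / (2 DE))

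| ICC | per TU | DE | pairwise | three-arm |
|---|---|---|---|---|
| 0.05 | 15 | 1.70 | 13.3% | 17.2% |
| 0.05 | 16.5 | 1.775 | 14.1% | 18.5% |
| 0.05 | 22 | 2.05 | 17.1% | 23.2% |
| 0.02 | 15 | 1.28 | 8.3% | 9.6% |
| 0.02 | 22 | 1.42 | 10.0% | 12.1% |
| 0.01 | 15 | 1.14 | 6.6% | 7.2% |
| 0.01 | 22 | 1.21 | 7.5% | 8.4% |

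A simulation (400,000 runs, six equal clusters, two per arm, random TU effect on the change score) gives 13.5% to 23.6% at ICC 0.05, in agreement. A nominal 95% pairwise interval at ICC 0.05 then covers about 83% (100 − 17.1) to 87% (100 − 13.3).

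**Multilevel model.** Six TUs minus three arms leaves 3 between-TU df. The critical values are t = 3.18 and F(2,3) = 9.55, against 1.96 for a large-sample test. In the same simulation at ICC 0.05, with 15 to 22 per TU:
- uncorrected large-sample tests reject 8-12% of the time under REML and 12-20% under ML (at ICC 0.01, about 5-6% and 7-8.5%);
- a test on TU means with 3 df rejects 5.0% at every ICC from 0 to 0.10;
- a REML model with t on 3 df, and the TU variance not allowed below zero, rejects only about 1%. It equals the TU-mean test when the estimated TU variance is positive and is conservative when that estimate is zero.

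**Power of the TU-mean test, 15 points, SD 20.** SE = 20 × √(DE / m). At ICC 0.05 and m = 22, SE = 20 × √(2.05 / 22) = 6.1 and the non-centrality is 15 / 6.1 = 2.46. Power is about 40% on t with 3 df. With 16 per TU it is about 35%. At ICC 0.01 it is about 58% (22 per TU) and 48% (16 per TU). A normal reference at ICC 0.05 and 22 per TU would give 69%, so most of the shortfall from 80% comes from having only 3 df.

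**The case against.** The best defence is that a cluster-aware analysis is already planned. The Methods end with a multilevel regression, name dedicated software for it, and give it the role of verifying the intervention effect. On that reading the ANOVA is a preliminary step and the abstract's wording is only loose condensation. Estimator and degrees of freedom are also details that a full protocol or analysis plan may settle.

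Much of this stands, and it rules out three stronger readings that a reader might infer:

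- *That the trial's true type I error is 13-23%.* That range needs ICC 0.05, which the protocol gives as an upper value, and it belongs to tests that ignore TU. No ICC for change scores is given. The 23% end also needs the three-arm test with all 22 per TU retained.
- *That the plan is to use ordinary regression.* Only the abstract says so. The Methods specify the multilevel model, so this is a contradiction to reconcile.
- *That the multilevel model will be tested with a large-sample Wald test.* The article states neither estimator nor reference distribution. The multilevel rates above are conditional on that choice.

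The paired tests, likewise, are presented as describing change over time and are not called tests of intervention effect.

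The ANOVA itself is not rescued. The article names it as the between-group comparison, at the same 0.05 level as everything else, and does not formally call the multilevel model primary. An analysis plan would have to override that sentence, not just add detail.

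**Conclusion.** Wrong as written. The stated between-group ANOVA does not fit a trial that randomises TUs, and the abstract and Methods disagree on the final model. For 15 to 22 per TU, the type I error of the ANOVA or its pairwise contrasts is about 13-23% at ICC 0.05, 8-12% at 0.02 and 7-8% at 0.01. It exceeds 5% at any positive ICC.

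The multilevel model is the right choice. It would be liberal as well at ICC 0.05 if tested without a small-sample correction, but the article does not say that it will be.

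The figures assume equal cluster sizes, no covariate adjustment, an ICC that applies to change scores and, for power, an SD of 20 for the change.

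**What to change.** 1. Name one confirmatory between-arm analysis. Either compare baseline-adjusted TU mean changes with a t-test on 3 df, or use the multilevel model with a random TU intercept (plus a participant level if all visits are modelled), fitted by REML with a small-sample t reference of about 3 df. State how a zero TU variance estimate is handled, since fixed 3 df is then conservative.
2. Label the repeated-measures ANOVA and the within-arm paired tests as descriptive.
3. Change the abstract to name the same multilevel model.

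Only the analysis text changes, but the consequence is more than wording. Intervals will be wider. Power for 15 points at ICC 0.05, by the TU-mean test, is about 40% with 22 per TU and about 35% after 25% loss; at ICC 0.01 it is about 48-58%. The REML version on fixed 3 df would have less. This limit comes from having two TUs per arm, and the sponsor should disclose it before analysis.
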